### Secondary endpoint analysis

Secondary endpoints measured by the accelerometer will be modeled similarly to the primary outcome measure. The association of the PROMIS Global 10 Survey score and activity will be quantified by the rank order correlation of the area under the curve for the incremental gain in activity over the 7 days (mean of the 7 days after transfusion/control visit minus the mean of the 3 days prior to the transfusion/control visit) and the PROMIS Global 10 Survey total score. We will conduct this on the entire data (transfusion and control visits) as well as with a partial correlation controlling for whether a transfusion was actually conducted.

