### Aims and objectives

#### Primary

In light of the ongoing equipoise regarding the efficacy of RBC transfusion in the ambulatory setting, the known risks associated with blood product administration, and the availability of innovative technologies that are able help to address these concerns, the primary aims of our proposed protocol are as follows:
**Specific aim 1**: to evaluate the impact of RBC transfusion on home functional status as assessed by physical activity metrics recorded by a wearable ActiGraph wGT3X-BT mHealth device. We hypothesize that the percent change in mean daily physical activity in the 7 days following randomization will be greater during the study periods where participants received an RBC transfusion than during the periods where an RBC transfusion was not received.
**Specific aim 2**: to evaluate the correlation between physical activity as assessed by the accelerometer and subjective functional status as assessed with the Patient-reported Outcomes Measurement Information System (PROMIS) Global 10 Survey. We hypothesize that there will be a direct correlation between physical activity as assessed by the device and the subjective functional status as assessed by the PROMIS Global 10 Survey.

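### The Aim 2 analysis correlates a gain in activity with an undifferenced PROMIS score, so it can hide the activity–function correlation that Aim 2 hypothesizes.

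*Protocol article*

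**What the plan says.** Protocol article, Aims and objectives (Primary): two aims are introduced with the words "the primary aims of our proposed protocol are as follows". The second hypothesizes that "there will be a direct correlation between physical activity as assessed by the device and the subjective functional status", the latter measured by the PROMIS Global 10. The hypothesis contains no change score.

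Protocol article, Secondary endpoint analysis: the association is to be quantified by the "rank order correlation of the area under the curve for the incremental gain in activity over the 7 days". The activity variable is spelled out as the "mean of the 7 days after transfusion/control visit minus the mean of the 3 days prior to the transfusion/control visit". The other variable is given as "and the PROMIS Global 10 Survey total score", with no baseline subtracted. On the observations used: "We will conduct this on the entire data (transfusion and control visits) as well as with a partial correlation". The partial correlation controls only for whether a transfusion was given.

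No other analysis relating activity to PROMIS is stated. The section names no test, significance level or p-value for this correlation.

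**The concern.** The two variables are on different footings. The activity variable is a within-person change around a visit; the PROMIS variable is a status. A habitually active participant with a high PROMIS score and a sedentary one with a low score can have the same gain, so the contrast that would show the device tracking function drops out of the activity variable.

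The pilot is partly meant to find out whether accelerometry is informative about function in this population. A near-zero coefficient could then be read as the device not reflecting what patients report, when the choice of variables produced it.

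A second, linked point is that each participant supplies up to two pairs, one per visit type, and the only adjustment named is for transfusion status. That adjustment does not address pairing within a person.

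**Working it through.** **Inputs from the protocol.** Evaluable participants: 24 (Sample size considerations: 12 per group × 2 groups). Planned: 24 × 1.25 = 30, which reproduces the stated 30. Visits per participant: up to 2, so up to 48 pairs at n = 24. Averaging windows: 3 days before and 7 days after each visit. The protocol gives no target correlation, variance or intraclass correlation (ICC) for Aim 2, so everything below that needs one rests on assumptions.

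**Step 1: gain with level against level with level.** Assumed model: true activity after a visit is S + V, where S is the stable person level (SD s) and V the visit-specific response (SD v), drawn independently at each visit. Day-to-day noise has SD d. The pre-visit mean is S plus noise of variance d²/3; the post-visit mean is S + V plus noise of variance d²/7. PROMIS correlates ρ = 0.5 with S + V.

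- Level with level: r = ρ × √[(s² + v²) / (s² + v² + d²/7)].
- Gain with level: S cancels from the gain, so r = ρ × v² / √[(s² + v²)(v² + d²/3 + d²/7)].

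Worked case s = 1, v = 0.3, d = 0.5:

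- Level: 0.5 × √(1.09 / 1.1257) = 0.49.
- Gain: 0.5 × 0.09 / √(1.09 × 0.2090) = 0.045 / 0.477 = 0.09.

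All cases, with the formula (product-moment scale) beside the mean pooled Spearman from 3,000 simulated trials of 24 participants:

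| s | v | d | Level, formula | Level, simulated | Gain, formula | Gain, simulated |
|---|---|---|---|---|---|---|
| 1 | 0 | 0.5 | 0.49 | 0.45 | 0.00 | 0.00 |
| 1 | 0.3 | 0.8 | 0.48 | 0.45 | 0.07 | 0.06 |
| 1 | 0.3 | 0.5 | 0.49 | 0.46 | 0.09 | 0.09 |
| 1 | 0.5 | 0.5 | 0.49 | 0.46 | 0.18 | 0.18 |
| 0.5 | 0.5 | 0.5 | 0.48 | 0.46 | 0.29 | 0.28 |

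The simulated values run a little lower mainly because a rank correlation is slightly smaller than the product-moment one. The planned coefficient is smaller in every case. It is zero only when there is no visit response, and reaches 0.28 only when the visit response varies as much as people do.

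**Step 2: two visits per participant.** With two pairs per person and no true association, the variance of a pooled correlation is multiplied by about 1 + ICC(activity) × ICC(PROMIS). A naive two-sided 5% test then has error 2 × [1 − Φ(1.96 / √that factor)]. Results for n = 24, PROMIS ICC 0.6 to 0.9, 40,000 simulated trials per setting:

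| ICC of activity variable | Factor | Formula | Simulated error |
|---|---|---|---|
| −0.2 | 0.88 to 0.82 | 3.7% to 3.0% | 3.8% to 3.1% |
| 0 | 1.00 | 5.0% | 5.0% to 5.1% |
| 0.1 | 1.06 to 1.09 | 5.7% to 6.1% | 5.8% to 6.1% |
| 0.5 | 1.30 to 1.45 | 8.6% to 10.4% | 8.3% to 10.3% |
| 0.8 | 1.48 to 1.72 | 10.7% to 13.5% | 10.5% to 13.4% |

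Controlling for transfusion changes these values by at most 0.4 percentage points, and n = 30 gives nearly the same results. A gain score has the stable level subtracted out, so its ICC may be near zero, which puts the planned variable in the upper rows. A level has a higher ICC, which puts the corrected variable in the lower rows.

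**The case against.** **Aim 2 does not use the word level.** This is fair. Specific aim 1 is framed as a percent change, and the Measures section says the design is after changes in activity. But a change reading would call for a change in PROMIS as well. Gain against status matches neither reading, and the section does not explain the pairing.

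**The attenuation depends on invented variances.** This stands as a limit on size. A coefficient of exactly zero requires that PROMIS does not follow the visit response at all, and Aim 1 hypothesizes that there is such a response. So the range 0.00 to 0.28 is the honest statement, not zero.

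**A level correlation has its own weakness.** This also stands. The Measures section derives energy expenditure from activity counts and body weight, so a between-person correlation of that metric partly reflects weight, which differencing reduces.

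**The role of Aim 2 is modest.** It is listed as a primary aim but analysed as a secondary endpoint, and the stated considerations for a larger trial do not name this correlation. That limits the consequences but leaves the mismatch.

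**A stronger reading to avoid.** A reader might infer that pooling two visits per person yields an invalid p-value. The documents do not support that. The section says the association is quantified and plans no test. It neither states nor excludes a participant-level interval, and an unseen analysis plan could supply one. For the gain score as planned, even a naive test may be close to 5%.

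**Conclusion.** The point holds for the choice of variables. The protocol fixes both explicitly, so an unseen analysis plan would have to depart from the text rather than fill a gap. Under assumed variances, n = 24 and a true level correlation of 0.5, an association that would show as about 0.45 with matched levels appears as roughly 0.00 to 0.28. The direction (attenuation) appeared in every scenario tried; the amount is illustrative.

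The pairing of visits is a supporting point, not a separate error. It matters little for the gain score if its ICC is near zero, and more once activity becomes a level: a naive pooled test would then have about 8% to 13% error if both ICCs are high (activity 0.5 to 0.8, PROMIS 0.6 to 0.9, all assumed). The two should therefore be settled together.

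**What to change.** Reword the Aim 2 paragraph in Secondary endpoint analysis:

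1. Main analysis: rank correlation of 7-day post-visit mean activity with the PROMIS score from the weekly telephone call covering those 7 days.
2. Secondary analysis: change in activity with change in PROMIS, only for visits with a pre-visit PROMIS score. The article documents no score before the first visit, so this may be restricted to the second.
3. Report within- and between-participant correlations separately, with intervals from a bootstrap that resamples participants and keeps both visits of a person together.
4. Report the same correlations for daily step count, already a secondary outcome, because energy expenditure is computed with body weight.

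The main analysis uses the continuous accelerometer record and the weekly calls already planned, so the cost is wording and a small amount of programming. The existing gain-with-level correlation can stay as a labelled exploratory result.

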### Intervention

Those randomized to transfusion will receive the standard-of-care-ordered RBC transfusion. This means that they will receive the transfusion as specifically ordered by their primary physician, typically one to two units of allogeneic RBCs. Those randomized to the no-transfusion arm will be discharged from the AIC without receiving an RBC transfusion. The patients who are randomized into the transfusion group will be crossed over into the no-transfusion group and the patients who are randomized into the no-transfusion group will be crossed over into the transfusion group at a subsequent visit. The time of this crossover for a given patient will be at their next scheduled transfusion that is no less than 1 week from the time of their most recent RBC transfusion in this trial.

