### Primary analysis

The primary outcome analyses will be performed using an “as treated” rather than an “intention-to-treat” analysis set while accounting for the crossover design. This approach is most appropriate for this pilot clinical trial, which primarily aims to understand home functional status as it relates to ambulatory RBC transfusion. For statistical comparisons, we will fit a random effects model that utilizes daily total energy expenditure as the dependent variable and days from transfusion or control visit (“placebo” visit where no transfusion was performed). For simplicity, we will include the mean daily measurements for the 3 days prior to the transfusion/control visit as covariates in the model, and consider the 7 days after transfusion/control visit in the model. This censoring of data beyond 7 days after the transfusion/control visit is to avoid carryover effects with the model. We will test the transfusion indicator by study day interaction, with adjustment for baseline activity, for the primary hypothesis. This parameter will quantify how the profile of activity differs with and without transfusion while accounting for the variation in activity between participants by means of the random effect and baseline adjustment. Contrasts will be constructed to quantify the difference in the change in activity between these visits.

Sensitivity analyses will attempt to model the change in activity levels in the days after transfusion. These exploratory models will consider a potential initial boost in activity with linear or exponential trends to account for the change in activity over the 7 days after transfusion. These models will also include subject random effect and account for time-series correlation. These analyses will be expanded to include all data measured over the 28-day period.

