In addition to the above concerns about efficacy and safety, it is important to remember that blood products are a precious resource. Considering data from 2011 [1], the available supply of whole blood/RBC units exceeded the number of transfused units by only 5.2%, with a trend in donation rates dropping 3–4% per year. An aging US population can only be expected to exacerbate the situation. Furthermore, the direct and indirect costs associated with blood product transfusion are rising [52]. Goodnough et al. [36] found that over a 5-year period, implementing a best-practice alert triggered for higher Hgb transfusions saved a large hospital US$1.3 million annually in purchasing costs alone.

With the above in mind, it is clear that deeper understanding of the true utility of RBC transfusion is of vital importance to the field. The randomized crossover clinical trial proposed here aims to provide preliminary information on the feasibility of measuring the efficacy of RBC transfusion in improving home functional status with a wearable activity monitor. The study, while it can be described as a pilot, is robust in that it utilizes a randomized crossover design, incorporates an objective measurement of activity based on accelerometer data, and includes patient-reported health status. This study will provide novel data that will aid in the elucidation of transfusion’s influence on ambulatory activity following outpatient transfusion.

In addition to the strengths of the trial noted above, we also acknowledge potential weaknesses of the protocol. Such limitations include concerns relating to the detectability of activity level in what may often be a sedentary population with variable daily activity levels, risk that the effect from transfusion may exceed the 1-week washout period, and difficulty in recruiting patients who will be willing to consistently wear a monitor for 28 days. Though we acknowledge these potential challenges, the insights gleaned will greatly facilitate the potential design and conduct of a future, more definitive, clinical trial. We look forward to seeing the results of this trial and to gaining important insight into this clinically relevant question.

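### The activity gain sets 7 days after a visit against 3 days before it, so any weekend effect enters the gain as removable noise that depends on the weekday of the visit

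*Protocol article*

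**What the plan says.** Under Secondary endpoint analysis, Aim 2 is assessed by the "rank order correlation of the area under the curve for the incremental gain in activity over the 7 days", where the gain is the "mean of the 7 days after transfusion/control visit minus the mean of the 3 days prior to the transfusion/control visit". It is correlated with the PROMIS total score over all visits, "as well as with a partial correlation controlling for whether a transfusion was actually conducted". Transfusion status is the only variable that this correlation is said to control for.

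Under Primary analysis the same 3-day mean returns as a baseline: "For simplicity, we will include the mean daily measurements for the 3 days prior to the transfusion/control visit as covariates in the model". The 7-day limit is explained by carryover alone: "This censoring of data beyond 7 days after the transfusion/control visit is to avoid carryover effects with the model".

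Under Intervention, the second visit takes place "at their next scheduled transfusion that is no less than 1 week from the time of their most recent RBC transfusion in this trial". The two visits therefore need not fall on the same weekday. The article names no weekday or weekend term. Its Discussion does acknowledge "what may often be a sedentary population with variable daily activity levels", but it describes no weekly pattern.

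**The concern.** The two halves of the gain cover different mixes of days. Where activity follows a weekly rhythm, part of the gain reflects the day on which the appointment fell and not any change in the participant.

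Aim 2 stands among the primary aims, and its analysis ranks these gains across visits and people. Even if each participant's two visits share a weekday, weekdays still differ between participants, so the error stays in the ranking. The pilot is also meant to show whether accelerometers can detect change and to supply a standard deviation for a later trial. Noise that could be removed makes the device look less sensitive and inflates the standard deviation of any change score.

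**Working it through.** **Plan's own figures.** The article gives no weekend effect and no daily standard deviation, so there is no figure on this point to reproduce. Its sample size (2 × 12 = 24; 24 × 1.25 = 30) reproduces and is not affected.

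**Inputs from the article.** Post window of 7 days, pre window of 3 days, 28 days of recording, at least 24 evaluable participants.

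**Assumptions.** Visits on Monday to Friday; complete windows; weekend activity differs from weekday activity by d, with d = -10, -20 or -30 (% of the daily mean). A busier weekend reverses every sign.

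**Gain with an unchanged routine.** Seven consecutive days contain 2 weekend days, whether counted from the visit day or the day after. Let k be the number of weekend days among the 3 days before the visit. Then

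gain = d × (2/7 - k/3)

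| Visit day | k | Gain | d = -10 | d = -20 | d = -30 |
|---|---|---|---|---|---|
| Mon, Tue | 2 | -0.381d | +3.8 | +7.6 | +11.4 |
| Wed | 1 | -0.048d | +0.5 | +1.0 | +1.4 |
| Thu, Fri | 0 | +0.286d | -2.9 | -5.7 | -8.6 |

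The largest difference between two visits with identical behaviour is (2/3)|d|, which is 6.7, 13.3 or 20 points. At d = 0 it is zero.

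**Share of day-to-day noise.** With visits spread evenly over Monday to Friday, k takes the values 2, 2, 1, 0, 0 and has variance 0.8. The artefact variance is 0.8 × d²/9, which is 8.9, 35.6 or 80. With independent days of standard deviation s, the noise variance of the gain is s² × (1/7 + 1/3).

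- s = 20: noise variance 190.5, so the artefact adds 5%, 19% or 42%.
- s = 30: noise variance 428.6, so it adds 2%, 8% or 19%.

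**Effect on the rank correlation.** Simulation with 200,000 draws per scenario, true rank correlation about 0.48, weekday activity set at 100, everything assumed. Each cell gives the correlation without, then with, the weekend pattern, using the 3-day baseline.

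| Daily SD, SD of true gain | d = -10 | d = -20 | d = -30 |
|---|---|---|---|
| 10, 5 | 0.284, 0.268 | 0.283, 0.230 | 0.285, 0.189 |
| 10, 10 | 0.397, 0.384 | 0.392, 0.351 | 0.393, 0.309 |
| 20, 5 | 0.163, 0.159 | 0.161, 0.150 | 0.165, 0.138 |
| 20, 10 | 0.278, 0.274 | 0.283, 0.267 | 0.281, 0.246 |

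The loss is below 0.02 at a 10% weekend drop, about 0.01 to 0.05 at 20%, and about 0.03 to 0.10 at 30%.

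**Primary model.** The 3-day mean is a covariate with an estimated coefficient and is not subtracted, so the gains in the first table do not carry over. On the outcome side, 7 complete days hold each weekday once, so a 7-day average contrast is free of the weekday effect. Day-specific contrasts are not. The day after a Friday visit is a Saturday and the day after a Tuesday visit is a Wednesday, so a participant with one visit on each carries a full d into the day-1 comparison. If both visits share a weekday, this cancels within the participant.

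**The case against.** The strongest reply is that nothing in the article shows a weekly rhythm. Most participants are on chemotherapy or are transplant recipients, and the Discussion expects many to be sedentary. With a flat week there is no artefact. This stands: the point is conditional on d.

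Second, the practical loss is small. The variance shares above compare the artefact with day-to-day noise only and leave out true variation in gain, so they overstate its share of the total. With about 48 visits from 24 participants, the standard error of a rank correlation is roughly 1/√47 = 0.15 even if visits are treated as independent, which is larger than every loss simulated. The short baseline has a cost of its own: with daily SD 20 and true-gain SD 10, a 7-day baseline gives about 0.33 against 0.28 for 3 days, before any weekend effect. This stands too.

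Third, the listed model terms are plainly abbreviated, and an analysis plan that is not shown could add a weekday term. That is fair for the primary model. It does not answer the gain, whose 7-versus-3 definition the article fixes itself.

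Fourth, the formula needs complete windows, while Data monitoring applies a minimum-wear rule for valid days and permits averaging whatever is available. With missing days the gain becomes d × (weekend share of valid post days - weekend share of valid pre days). That alters the size of the artefact without removing it.

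Two stronger readings do not hold. A reader might infer that the definition favours transfusion or control. Sequence is randomised and nothing ties visit weekday to arm, so the article gives no ground for that. A reader might also carry -0.38d and +0.29d into the primary contrast, which the covariate role of the baseline rules out.

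**Conclusion.** The point holds as a minor precision issue for Aim 2. The weekday dependence of the gain is plain arithmetic. Its size rests on a weekend difference that the article does not give, on weekday visits and on complete windows. Under an assumed difference of 10% to 30%, the false gain runs from +11.4 to -8.6 points across visit days, and the rank correlation is modestly weakened, typically by 0.01 to 0.05 at a 20% difference. The primary model takes on partial noise only, in the baseline covariate and in the day-by-transfusion profile, and only where a participant's two visits fall on different weekdays. No arm is favoured and the planned test is not invalid.

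**What to change.** In Primary analysis, add a weekend (or day-of-week) fixed effect to the daily model. In Secondary endpoint analysis, compute both means of the gain from valid daily values adjusted for a weekend effect estimated from all valid recorded days of the 28-day period. This puts both windows on the same mix of days and also handles windows with missing days. State it before the data are analysed.

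A full-week baseline would also bring the false gain to exactly 0. It needs seven recorded days before each visit, however, and where the visits are only a week apart it would largely coincide with the previous post-visit window. The adjustment is the easier change.

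Cost: analysis wording and about one degree of freedom for a weekend term, against up to 14 outcome days per participant. No new data, visits or participants are needed. There are two limits. If visits cluster on a few weekdays, the weekend term overlaps with day since visit and those terms lose some precision. A common weekend effect also does not remove routines that differ between people.
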